## Abstract

**Background:**

Physical rehabilitation is required to enhance functional outcomes and overall recovery following total knee arthroplasty (TKA). However, there are no universally accepted clinical guidelines available to consistently structure rehabilitation for TKA patients. A common method is rehabilitation provided in an outpatient setting, on a one-to-one treatment basis. This method is resource-intensive and outcomes must be compared to less costly alternatives such as home-based rehabilitation. The current study will analyse a novel home-based rehabilitation program. The Maxm skate is a portable, lower-limb, postoperative, rehabilitation exercise device for individual use in a hospital or home-based setting. This study was developed to compare the safety, efficacy and cost-effectiveness of the Maxm Skate rehabilitation program to standard rehabilitative care following TKA. The primary outcome is the range of motion (ROM) achieved by patients who received the Maxm Skate program compared to standard care at three months post TKA. Secondary outcomes include patient-reported outcomes, costs and functional evaluations which will be collected at multiple time-points up to 12 months after TKA.

**Methods:**

This is a single-blinded, randomised controlled trial (RCT) in which 116 eligible participants consented for primary TKA will be randomly allocated to receive either the Maxm Skate rehabilitation program or standard rehabilitative care. Fifty-eight participants per group will provide 90% power (α = 0.05) to detect 10° of difference in ROM between groups at three months after TKA, assuming a within-group standard deviation of 16° and allowing for 5% loss to follow-up. Participants randomised to the Maxm Skate group will use the skate device and accompanying iOS App and sensors to complete rehabilitation exercises, as outlined in the *Maxm Skate Rehabilitation Guide*. Outcomes will be compared to those receiving standard rehabilitative care.

A blinded physiotherapist will evaluate functional outcomes preoperatively and at 2, 4, 6, 12, 26 and 52 weeks after TKA. The functional assessment will include measures of knee ROM, pain, isometric knee strength, balance and knee/thigh circumference. Limited measures will also be assessed at day 2 postoperatively by an alternate, unblinded physiotherapist. Clinical outcome measures will be administered preoperatively and at 6, 12 and 52 weeks postoperatively. An economic evaluation will be conducted and participants will be screened for adverse event occurrences from the time of consent to 12 months postoperatively.

**Discussion:**

This RCT will be the first to investigate the safety, efficacy and cost-effectiveness of the home-based Maxm Skate Rehabilitation program, in comparison to standard rehabilitative care following primary TKA.

**Trial registration:**

Australian New Zealand Clinical Trials Registry, ACTRN12616001081404p. Registered on 11 August 2016.

**Electronic supplementary material:**

The online version of this article (10.1186/s13063-018-3102-9) contains supplementary material, which is available to authorized users.

## Background

Primary total knee arthroplasty (TKA) is an increasingly common surgical intervention used to alleviate pain and physical dysfunction associated with end-stage degenerative joint disease. Following surgery, patients experience lower-extremity muscle weakness and commonly require physical rehabilitation to enhance functional outcomes and overall recovery [1, 2]. While TKA is a successful procedure for many patients, up to 15–20% of patients remain unsatisfied [3, 4]. Limited postoperative range of motion (ROM), which is often associated with arthrofibrosis, may be one factor associated with patient dissatisfaction. The recorded incidence of arthrofibrosis after primary TKA varies in the literature, in the range of approximately 1–13% [4–6]. When it occurs, it is a significant cause of patient dissatisfaction associated with poor ROM and is a causative factor of revision TKA [5, 6]. Therefore, as limited ROM is an early indicator of potential arthrofibrosis, rehabilitation that enables ongoing flexion/extension exercises and ongoing collection of such progress, may improve early detection of arthrofibrosis and as such appropriate rehabilitative management before the need for revision surgery. In addition, it is well established that daily activities including climbing stairs and standing from a chair require 90–120° of flexion, kneeling and squatting 110–165°, 135° of flexion to lift from a bath and > 150° for yoga or gardening [7–9]. However, patients rarely achieve > 120° of flexion post TKA and 110° of flexion is an optimal goal for rehabilitation following TKA [9–11]. At present, there are no universally accepted or widely implemented clinical guidelines available to consistently structure patient rehabilitation following TKA [12–14]. Consequently, rehabilitative protocols are not standardised and regularly based on institution-, surgeon- or occasionally, patient-specific preferences [1, 2, 12]. This lack of uniformity in the mode of rehabilitation results in therapy of different types, frequency, intensity and duration across sites and countries [1, 2].

In Australia, rehabilitation most commonly provided is in an outpatient setting, on a one-to-one treatment basis [12]. Outpatient physiotherapy in a clinic-based setting is beneficial as a physiotherapist can monitor progress and modify therapy; however, such methods are resource-intensive and impose a significant cost burden [2]. Further concerns include patient transportation to clinics following surgery and accessibility to qualified rehabilitative specialists.

In 2016, the number of primary TKA procedures performed in Australia increased by 139.8% since 2003 and by 2.8% compared to 2015 [15]. Such trends suggest that TKA use will continue to rise, bringing concern of the sustainability and economic impact of one-to-one rehabilitation commonly employed. There is a need to determine whether such outpatient physiotherapy yields superior outcomes compared to less costly alternate forms such as group-based, home-based or tele-rehabilitation.

Several randomised controlled trials (RCT) have considered the influence of outpatient physiotherapy on functional outcomes following TKA. Mockford et al. [16] and Rajan et al. [17] both concluded no significant difference in ROM achieved between patients who did and did not receive outpatient physiotherapy 12 months after TKA. However, methodologically short-comings, and limited descriptions of the standard outpatient physiotherapy provided, caused a literature reviewer to suggest that conclusions from these studies were not supported [2]. A methodologically robust RCT found that one-to-one outpatient treatment provided over a six-week period did not provide superior self-reported or performance-based outcomes, compared to group-based or monitored home programs up to 12 months after TKA [18]. Furthermore, a recent meta-analysis demonstrated no difference in knee ROM and short-term functional improvements between outpatient physiotherapy in a clinic-based setting and non-supervised home-based exercise regimens following discharge after TKA [19].

The common provision of one-to-one therapy is not currently supported over more economical home-based rehabilitative methods of which elicit similar self-reported, functional and performance-based outcomes [18, 20]. The current study will analyse a novel home-based rehabilitation program as compared to the standard rehabilitative care options available to patients. As detection of arthrofibrosis is typically first observed through reduced postoperative ROM, it is particularly important to this study to collect ROM data. Furthermore, early detection of poor ROM (three months) may enable implementation of appropriate rehabilitation before the requirement of manipulation under anaesthesia (MUA) or revision surgery.

The Maxm Skate device is a portable, lower-limb, postoperative and post-injury rehabilitation exercise device for individual use in a hospital or home-based setting. The Maxm Skate intends to facilitate rehabilitation and conditioning of the lower limb through graded therapeutic exercise with the aim to promote tissue healing, remodelling and strengthening. It allows the patient to perform strengthening exercises with minimal joint loading during their rehabilitation period.

The Maxm Skate package comprises the Skate device and rope (for assisted active motion and resistance training), sensors, iOS Application (App) and website. The Skate device is accompanied by two sensors and a mobile App which are designed to provide real-time, objective data on exercise and rehabilitation progress, in particular ROM following each home-based exercise therapy session. This sensor technology also enables the clinician to monitor accurate compliance and ROM data (Flexion and Extension) remotely.

This clinical trial is the first to compare the safety, efficacy and cost-effectiveness of the Maxm Skate rehabilitation package to standard rehabilitative care up to 12 months after TKA.

### Objectives

The primary objective of this RCT is to assess the ROM achieved by TKA patients whom received the Maxm Skate rehabilitation package compared with standard rehabilitative care, three months postoperatively.

Secondary objectives include the comparison of functional, clinical and performance-based outcome measures between the Maxm Skate and standard rehabilitative care groups at multiple times points, up to 12 months after TKA. An economic evaluation assessing the relative cost-effectiveness of the Maxm Skate rehabilitation package compared to standard care will be conducted; patients will be screened for adverse event (AE) occurrences and complications from the time of consent to one year postoperatively.

## Methods/Design

This is a single-blinded RCT comparing the safety, efficacy and cost-effectiveness of the Maxm Skate Rehabilitation Program to standard rehabilitative care following TKA.

### Study setting

The study will be coordinated by the International Musculoskeletal Research Institute Inc. at the study site, Flinders Private Hospital (FPH), Bedford Park, South Australia.

### Recruitment and selection criteria

Consecutive patients consented for elective primary TKA at a single orthopaedic surgeon’s private clinic will be screened for eligibility. The treating surgeon ([name]) will screen all patients against the selection criteria and document reasons for ineligibility in the patient screening log. Study inclusion criteria include:The patient requires a primary TKA due to non-inflammatory degenerative joint disease (e.g. osteoarthritis and traumatic arthritis) or inflammatory joint disease (e.g. rheumatoid arthritis).The patient must understand the conditions of the study and be willing and able to provide written informed consent.The patient is a skeletally mature man or a non-pregnant woman, aged ≥ 30 years.The patient agrees to comply with the specified preoperative and postoperative study requirements.

Study exclusion criteria include:The patient has an emotional or neurological condition that would pre-empt their ability to participate in the study including mental illness, intellectual disability and drug or alcohol abuse.Any patient who is unable to meet the requirements of the use of the Maxm Skate Rehabilitation Device.The patient is unable to perform home exercise program without supervision or assistance.

A clinical nurse or authorised delegate will invite eligible patients to come in to discuss the study. Patients will be informed of the study purpose and the potential risks and benefits known, or that can be reasonably predicted, as outlined in the Participant Information Sheet.

The patient will then be given the opportunity to ask any clarifying questions and invited to complete the consent form, indicating their understanding of the study and consent for participation. Following consent, participants will be randomised and baseline measures obtained. The randomisation number will be used to provide anonymous identification of the participant on study documents from there forth.

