### Randomisation and blinding

The randomisation schedule will be prepared using numbered and sealed, opaque envelopes. Participants will be randomly allocated in a 1:1 ratio to either the ‘Maxm Skate Rehabilitation Program’ or the ‘Standard Rehabilitative Care’ group. Block randomisation in groups of four will be used to ensure balance in the two groups. Randomisation will also be stratified by gender to ensure balance between groups for each gender. We note that the number of women undergoing TKA for osteoarthritis has been shown to be greater in Australia [21]. In addition, studies have demonstrated that there are differences between men and women in muscle and physical function recovery after TKA [22, 23].

The study will be single-blinded with blinding of study investigators but not participants. Participant randomisation to either Maxm Skate or Standard Care will be performed by the unblinded Study Coordinator, who will hold the treatment allocation code in confidence. The statistician will be blinded to the treatment allocation code when performing all analyses. Functional evaluations and performance tests will be conducted by a trained physiotherapist ([name]) who will be blinded to group allocation. This blinded physiotherapist will conduct all functional evaluations, excluding postoperative day 2, due to practical constraints. Non-blinded ward-based physiotherapists will conduct the day 2 assessments, as well as the preoperative Maxm Skate education session for participants allocated to the Maxm Skate group.

Due to the nature of the intervention there is a potential for participants to disclose, or physiotherapist to gauge, which group the participants are assigned. Participants will be educated and instructed not to advise the physiotherapist or treating surgeon of their group assignment at the time of their consent and randomisation with the unblinded Study Coordinator. However, if participants are concerned about their rehabilitative progress and feel it is necessary to discuss this with their treating surgeon, they will be able to do so. The breaking of blinding will be collected and reviewed during data analysis.

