##### Preoperative phase

Participants will attend a preoperative device education session where they will be introduced to the Maxm Skate program by a physiotherapist. Participants will be given a description of the functionality, set up and safe usage of the Maxm Skate device and sensor, and educated on the Maxm Skate exercise program. Following this presentation, participants will be issued with a rehabilitation guide to familiarise themselves with the postoperative exercise program and given the opportunity to trial the skate package.

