#### Functional evaluations

The following functional evaluations will be performed by a blinded physiotherapist preoperatively and at 2, 4, 6, 12, 26 and 52 weeks after TKA. Some measures will also be assessed at day 2 postoperatively; however, these measures will be taken by an unblinded ward physiotherapist. Functional evaulations are illustrated in Fig. 2.

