##### Joint range of motion and the Visual Analogue Scale for Pain in flexion and extension

In a seated position, active joint ROM in flexion and extension will be measured using a standard goniometer. Furthermore, pain at end-of-range flexion and extension will be measured using the Visual Analogue Scale (VAS) for Pain. Recovery in knee ROM has been found to plateau 12 months after TKA, therefore end-of-study has been selected to be 12 months postoperatively [28]. Both measures will also be assessed at day 2 after TKA.

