### Statistical methods

All analyses will be conducted on an intention-to-treat basis and results reported in accordance with CONSORT guidelines [39]. The primary endpoint is the ROM at three months and differences between groups will be assessed using an independent two-sample t-test with log-transformation of the outcome, if necessary, in order to meet the assumptions of normality. If normality is not achieved using transformation, then the Mann–Whitney U test will be used. Differences between groups for the clinical performance tests (30-s Chair-stand and 4 × 10 m Fast Paced Walk Test) and data collected on scales such as the OKS will also be assessed using a two-sample t-test or Wilcoxon Rank sum test if normality is not achieved. Baseline characteristics, including ROM, will be accounted for in a sensitivity analysis using mixed effects models that will also account for any missing data. Where > 10% of data are missing, multiple imputation using chained equations will also be used. Functional evaluations that are assessed at multiple time points will also be assessed using mixed effects models with an interaction term between group and visit used to determine differences in group effects across time. Two-sided hypothesis tests will be performed for each outcome with a type-1 error rate of alpha = 0.05 used for determining statistical significance.

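### Baseline measures are listed after randomisation, when participants already know their group, so the baseline-adjusted sensitivity analysis may use values influenced by allocation

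*Protocol article*

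**What the plan says.** All references are to the protocol article.

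- **Order.** Recruitment and selection criteria: "Following consent, participants will be randomised and baseline measures obtained". Randomisation is named first.
- **Knowledge of allocation.** Randomisation and blinding: "The study will be single-blinded with blinding of study investigators but not participants". Participants are "instructed not to advise the physiotherapist or treating surgeon of their group assignment at the time of their consent and randomisation", so they know the assignment by then.
- **Baseline assessor.** The section on functional evaluations states: "The following functional evaluations will be performed by a blinded physiotherapist preoperatively and at 2, 4, 6, 12, 26 and 52 weeks after TKA".
- **ROM measure.** The section on joint range of motion and pain: "In a seated position, active joint ROM in flexion and extension will be measured using a standard goniometer".
- **Contact with the device.** Preoperative phase: Skate participants attend an education session before surgery and are "given the opportunity to trial the skate package". The text does not say whether this comes before or after baseline measurement.
- **Use of baseline.** Statistical methods: "Baseline characteristics, including ROM, will be accounted for in a sensitivity analysis", by mixed effects models. The primary comparison is a two-sample t-test on three-month ROM with no baseline term.

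**The concern.** A baseline value is a safe covariate when allocation cannot have influenced it. Here the stated order allows it to. Active ROM depends on how hard and how far the participant is willing to move. Maximal strength, chair-stand and walk tests depend on effort, and OKS, KOOS, EQ-5D-5L and PASS are self-reported. Someone who is pleased or disappointed with the allocation may perform or answer differently. Blinding the physiotherapist does not prevent that.

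If measured baseline ROM differs between groups because of allocation, adjusting for it shifts the estimated group difference. The adjusted model is the plan's stated way of accounting for baseline differences and missing data, so it is what a reader would use to judge whether the primary result is robust. Analysis cannot recover an uninfluenced baseline afterwards.

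**Working it through.** **1. The plan's own figure.** Inputs from Sample size: difference 10°, SD 16°, two-sided alpha 0.05, power 90%.

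- Normal approximation: n = 2 × (1.960 + 1.282)² × (16/10)² = 53.8, so 54 per group.
- t-test: 54.8, so 55 per group, with power 0.901.
- Allowing for 5% loss: 55/0.95 = 57.9, so 58 per group and 116 in total.

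The stated 110 and 116 reproduce, and this point does not depend on them.

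**2. Bias formula.** Let *s* be the allocation-related shift in measured baseline ROM in one group and *b* the slope of three-month ROM on baseline. If the shift affects the baseline measurement only and does not carry through to three months:

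bias in adjusted difference = −*b* × *s*

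**3. Numbers.** The documents give neither *b* nor *s*, so both are assumed.

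| Slope *b* | Shift 2° | Shift 5° |
|---|---|---|
| 0.3 | −0.6° | −1.5° |
| 0.5 | −1.0° | −2.5° |
| 0.7 | −1.4° | −3.5° |

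The signs are for a baseline shifted upward in the Skate group. They reverse for a downward shift.

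**4. Scale.** With 55 per group, the unadjusted 95% half-width is 1.982 × 16 × √(2/55) = 6.05°. Adjustment narrows it to about 6.05 × √(1 − r²), which is 5.8° at r = 0.3 and 4.3° at r = 0.7. The bias is therefore largest where the adjusted interval is narrowest.

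**5. Simulation.** There were 4,000 runs per scenario, with 55 per group and SD 16° at both times, so slope equals correlation. The shift was upward in the Skate group.

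| Analysis | Shift | Type I error (true effect 0) | Power (true effect 10°) |
|---|---|---|---|
| Adjusted | 0 | 0.046–0.051 | 0.925–0.996 |
| Adjusted | 2° | 0.051–0.088 | 0.881–0.975 |
| Adjusted | 5° | 0.081–0.343 | 0.800–0.840 |
| Unadjusted t-test | 0 to 5° | 0.044–0.059 | 0.892–0.907 |

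Ranges run over correlations 0.3, 0.5 and 0.7. The unadjusted t-test stays at its nominal level and planned power throughout.

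**6. QALYs.** Suppose QALYs are an area under the curve (assumed) over the EQ-5D-5L times in Patient-reported outcome measures: preoperative, 6 weeks, 12 weeks and 12 months. The preoperative value then has weight ½ × 6/52 = 0.058 years. Assumed utility shifts of 0.02 to 0.10 would move QALYs by about 0.001 to 0.006.

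**The case against.** The strongest reply is that the primary result is untouched. That stands: a reader might infer from the order of events that the three-month ROM comparison is biased, but that test uses no baseline value.

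Three other stronger readings also go beyond the documents:

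- **All baseline measures act as covariates.** Only ROM is named. The performance tests and scales such as the OKS are to be compared by unadjusted t-test or rank test.
- **The effect is wrong by the full shift.** That would be true of a change-from-baseline contrast, but no change-score analysis is explicitly planned. A group-by-visit model that took the preoperative visit as a response would carry the full shift in contrasts against that visit, but the text does not say that the visit is included.
- **Skate participants have used the device before baseline.** The education session is preoperative, but its place relative to baseline is not stated.

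It can also be said that the sentence joins randomisation and baseline with *and*, not *then*, and that the schedule figure is not available here. This weakens certainty about actual practice. However, nothing in the text available places baseline before disclosure. If baseline is in fact taken first, the sentence misdescribes the design and still needs correcting.

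Finally, the physiotherapist is blinded at the preoperative visit, and breaks in blinding are recorded. This limits the assessor route but leaves participant effort and self-report.

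**Conclusion.** The concern holds in limited form. As written, effort-dependent and self-reported baseline values may be collected after participants know their group. The primary t-test is unaffected. The exposure lies in the baseline-adjusted sensitivity analysis, any repeated-measures model that includes the preoperative visit, the baseline comparability table and, to a small degree, QALYs that start from the preoperative EQ-5D-5L.

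On assumed slopes of 0.3 to 0.7 and shifts of 2° to 5°, the bias in the adjusted ROM difference is about 0.6° to 3.5°. Its direction is unknown, and there may be no shift at all. The change is worth making because it is cheap and removes the question by design, not because the main result is in danger.

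**What to change.** Amend Recruitment and selection criteria so that the order is: consent; all baseline questionnaires and the blinded preoperative functional evaluation; then opening of the envelope and disclosure of allocation. State in Preoperative phase that the Skate education session follows. Align Randomisation and blinding, which ties the non-disclosure instruction to a joint consent and randomisation contact.

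Gender is the only stratification factor and is known at consent, so nothing in the scheme requires early randomisation. The sample size stays at 58 per group, and the allocation-induced baseline shift becomes zero by design.

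The cost is a short amendment and some scheduling. Randomisation moves to the end of the preoperative assessment or after it, so the Study Coordinator and the blinded physiotherapist must coordinate visits. The article does not say whether these contacts already fall on one day, so an extra contact cannot be ruled out.

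For anyone already enrolled, record whether baseline preceded disclosure. If the order cannot be changed, limit covariate adjustment to variables fixed before allocation, such as age, gender and diagnosis.

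### Using the randomisation number as participant ID, with a published block of four within gender, can let one known allocation inform the blinded physiotherapist about others in the block

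*Protocol article*

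**What the plan says.** The identifier is fixed under Recruitment and selection criteria: "The randomisation number will be used to provide anonymous identification of the participant on study documents from there forth". Patients consent, are then randomised, and then have baseline measures taken.

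The section Randomisation and blinding gives the rest of the mechanism:

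- Concealment: "The randomisation schedule will be prepared using numbered and sealed, opaque envelopes".
- Ratio and block: "Participants will be randomly allocated in a 1:1 ratio", and "Block randomisation in groups of four will be used to ensure balance in the two groups".
- Stratification: "Randomisation will also be stratified by gender to ensure balance between groups for each gender".
- Assessor: "This blinded physiotherapist will conduct all functional evaluations, excluding postoperative day 2, due to practical constraints".
- Acknowledged risk: "there is a potential for participants to disclose, or physiotherapist to gauge, which group the participants are assigned".
- Safeguards: "Participants will be educated and instructed not to advise the physiotherapist or treating surgeon of their group assignment". The unblinded Study Coordinator holds the allocation code, and breaks of blinding are to be collected and reviewed at analysis.

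The Data management section has study data entered directly on the Case Report Form. The primary endpoint, ROM at three months, rests on active flexion and extension read with a goniometer (Functional evaluations; Statistical methods).

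**The concern.** Participants know their group, so blinding of the single assessor is the main protection for a primary endpoint that the assessor reads. The randomisation number is not a neutral label. If it shows a participant's place in the allocation sequence, then together with gender, which any assessor can see, it shows which four participants share a block of two and two. Anything learned about one of them is then also information about the other three, including those who followed the instruction to stay silent.

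This route operates after allocation, so sealed opaque envelopes do not close it. The safeguards described deal with a participant's own disclosure. An improved guess about a silent blockmate is not an event that anyone would naturally record as a break of blinding.

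**Working it through.** **The plan's own figures.** The protocol gives no figure for the predictability of allocation, so there is none to reproduce on this point. The sample size is not in dispute: 55 per group gives 90.1% power (noncentral t; difference 10°, SD 16°, two-sided 5%), and 110/0.95 = 115.8, which rounds up to 116.

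**Inputs from the protocol.** Block of four, 1:1, hence two and two; strata by gender; 116 participants; one blinded assessor for every functional evaluation except day 2.

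**Assumptions not in the protocol.**
1. Numbers run in sequence within gender, so block membership can be read from number and gender.
2. The number is on the physiotherapist's forms.
3. The physiotherapist knows the block size.
4. Blocks are complete.
5. Each participant's group becomes known independently with probability p before the 12-week reading. No rate is given, so p = 10%, 20% and 30% are shown.

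**Step 1: what known allocations reveal.** A block has six possible sequences of two Skate (S) and two control (C).
- One known, say the first is S: SSCC, SCSC and SCCS remain. Any other given member is C in 2 of 3, so the probability moves from 1/2 to 2/3. No one is known for certain.
- Two known in the same arm (1/3 of pairs): one sequence remains, and the other two are certain.
- Two known in different arms (2/3 of pairs): the other two return to 1/2 each.
- Three known: the fourth is certain.

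**Step 2: a silent participant.** Take a silent participant in arm A, whose blockmates are one more A and two Bs.

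| Blockmates known | Probability | Best guess correct |
|---|---|---|
| none | (1−p)³ | 1/2 |
| the other A only | p(1−p)² | 0 |
| one B only | 2p(1−p)² | 1 |
| the other A and one B | 2p²(1−p) | 1/2 |
| both Bs, with or without the other A | p² | 1 |

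Accuracy = 0.5(1−p)³ + 2p(1−p)² + p²(1−p) + p². The allocation is certain with probability p².

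- p = 0.1: 0.3645 + 0.162 + 0.009 + 0.01 = 0.5455; certain 0.01.
- p = 0.2: 0.256 + 0.256 + 0.032 + 0.04 = 0.584; certain 0.04.
- p = 0.3: 0.1715 + 0.294 + 0.063 + 0.09 = 0.6185; certain 0.09.

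**Step 3: as head counts.** Of 116, the silent participants number about 104, 93 and 81 (116 × 0.9, 0.8, 0.7). Those known for certain through the block are then about 1, 4 and 7.

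**Step 4: why accuracy is the measure to quote.** The share of silent participants whose odds move at all is 3p(1−p)² + p², or 25%, 42% and 53%. That share includes p(1−p)², or 8%, 13% and 15%, whose odds move towards the wrong arm. Best-guess accuracy nets this out.

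**The case against.** Several links are inferred. The protocol says that the envelopes are numbered, but not how the numbers map to gender or block. It does not say what the physiotherapist's form displays, or whether blinded staff know the block size. A journal article may leave such details to the full protocol. This stands, and it is why the point is conditional. The conditions are nevertheless the ordinary reading: numbered envelopes in gender-stratified blocks are usually sequential, the Case Report Form is a study document, and the block size is in print.

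The effect is second-order. At p = 20%, a fifth of participants are known directly, while only 4% of the rest become certain through the block. The assessor would also have to keep track of numbers, gender and past disclosures over about 29 blocks (116/4). Disclosures can occur up to week 52, and one that follows a blockmate's 12-week reading cannot affect that reading. All of this stands. If p is taken as the rate over the whole follow-up, the figures above are upper bounds.

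The identifier is not the only source of order. Participants are randomised before baseline measures, so one assessor might infer the sequence from attendance. This also stands, and it affects the remedy.

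A reader might infer that one disclosure reveals the whole block, that the number appears on every document, or that silent participants will be analysed as still blinded. The protocol supports none of these. One disclosure gives 2/3. The sentence refers to study documents without saying all of them. The only commitment on unblinding is to collect and review breaks.

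**Conclusion.** The point holds as a conditional weakness in the protection of assessor blinding. It is not a contradiction or a wrong figure. If the numbers are sequential within gender, visible on the physiotherapist's forms and read by someone who knows the block size, the probability for each blockmate goes from 1/2 to 2/3 after one known allocation, and to certainty after two in the same arm. On average the gain is modest: roughly 5, 8 and 12 percentage points in guess accuracy at the three assumed rates. A reader might go on to infer a bias in measured ROM. The documents give no basis for expressing this in degrees, power or type 1 error, and none is claimed. Because the endpoint is assessor-read and the repair costs almost nothing, the change should be made.

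**What to change.** Replace the identifier sentence under Recruitment and selection criteria with wording such as: *Participants will be identified on all documents seen by blinded staff by a non-sequential study ID that carries no information on enrolment order, gender or block. The randomisation number, and its link to the study ID, will be kept only in the unblinded Study Coordinator's log.*

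The ID must be non-sequential. With an ID in enrolment order, an assessor who sees gender could count participants within gender and recover the blocks.

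Because visit order could still reveal the sequence, also use varied block sizes, not disclosed to blinded staff, for any allocations still to be generated.

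The cost is one linking column in a log held by someone who already holds the code, and slightly looser balance within gender. With blocks of four the arms within a gender never differ by more than 2; with varied sizes the limit is half the largest block. Sample size and analysis are unchanged.
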